### Power and sample size

2.4

Assuming 20% attrition and a Bonferroni correction for two co-primary outcomes (2-sided alpha 0.025), we estimate that 1,130 participants (565 participants in each treatment group) are needed for 95% or greater power to detect a 2.5 unit difference (25% of a standard deviation, or T-score of 2.5) for each of the co-primary outcomes in the overall population. The minimum detectable difference in T-score of 2.5 falls well within the T-score minimal clinical important difference (MCID) of 2–5. The 95% power for the primary outcomes was selected to allow the calculated sample size to also provide 80% power to detect a 7.5% absolute reduction in 30-day risk of death or re-hospitalization (from 30% to 22.5%) and 90% power to detect a 10% reduction.

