#### Primary outcomes

2.10.1

Patient and caregiver engagement activities indicated the need for two co-primary outcomes for the clinical trial:1.Change in participant anxiety from baseline (enrollment to 30 days post-discharge).2.Change in participant informational support (enrollment to 30 days post-discharge).

Informational support refers to the ability to obtain advice, guidance, suggestions, or useful information.

We will use the National Institutes of Health (NIH) PROMIS measures for our co-primary outcomes, since the development and validation of PROMIS scales have been extensively documented [27]. The PROMIS emotional distress-anxiety short form (version 1.0 SF4a, 4 items) will be used to assess participant anxiety in the previous 7 days. The PROMIS informational support short form (version 2.0 SF4a, 4 items) will be used to assess informational support among study participants in the previous 7 days. For PROMIS measures, raw scores for each measure will be re-scaled into a standardized T-score with a mean of 50 and standard deviation of 10 for the US general population [27,32,33]. Higher PROMIS T-scores indicate more of the concept being measured (e.g., higher anxiety T-scores indicate more anxiety). Studies suggest that a 2- to 5-unit or greater difference in T-scores is likely to be the MCID, though the MCID following hospital discharge in the target population has not been established.

Using PROMIS measures confers several distinct advantages: 1) *Comparability*—measures have been standardized to be patient-centered, rather than disease-specific, permitting comparisons of patient outcomes between the Navigator and Usual care groups despite enrolling patients with multiple conditions; 2) *Reliability* and *Validity*—metrics for each domain have been rigorously reviewed and tested; 3) *Flexibility*—PROMIS measures can be administered in a variety of ways (in person, telephone, or via computer adaptive testing); for PArTNER, the baseline visit occurred while the patient was in the hospital, so administration was in person. Follow-up visits were performed by telephone to minimize participant burden (a key principle in effectiveness trials); and 4) *Inclusiveness*—PROMIS encompasses all people, regardless of literacy, language, physical function, or life course.

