All analyses will be conducted using a modified intention-to-treat principle, in which we ignored the individual with the missing data for the co-primary outcomes (complete-case analyses). To assess the sensitivity of results to the complete-case analyses, we will conduct multiple imputations under a missing at random (MAR) assumption [34]. We will also conduct multiple imputations under a missing not at random (MNAR) assumption under a joint selection model of outcome and missingness and employ Bayesian analyses for each of the two co-primary outcomes. Our multi-tiered approach to missing data will be used to determine if the Navigator intervention effects are qualitatively maintained across various approaches to handling missing data. We will also conduct per-protocol analyses (PPAs) for the primary outcome. In the PPAs, the Navigator intervention will be considered per-protocol if the participant received both hospital and home-based components of the CHW-led interventions and at least one peer-coaching call. We will employ a 2-sided Bonferroni-corrected alpha of 0.025 (and 97.5% confidence intervals, CIs) for the two co-primary outcomes in the multivariable analyses, and a 2-sided alpha of 0.05 (and 95% CIs) for all other hypothesis tests.

We will also conduct exploratory analyses to assess the potential for heterogeneity of treatment effects for the primary outcome by examining the consistency of the adjusted differences in pre-specified subgroups (across levels of each baseline characteristic) in a series of linear regression models with covariates that included the treatment-group indicator, the treatment-by-subgroup interaction terms, and all other covariates in the multivariable models. We will also collect a limited number of baseline characteristics in keeping with information that is routinely collected on hospitalizations and that have been associated with hospital readmissions at MSIs [35]. The p-values for consistency of adjusted differences in linear or logistic regression models across subgroups will be determined by Wald chi-squared tests. The PArTNER study was not specifically powered to assess heterogeneity of treatment effects, so all such analyses should be considered exploratory. Due to multiple hypothesis tests, we will employ Bonferroni corrections to reduce the risk of a type 1 error.

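### A Holm step-down would serve the two co-primary outcomes better than the flat 0.025 Bonferroni tests, at the same 5% family-wise error and sample size

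*Protocol article*

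**What the plan says.** Section 2.10.1 (Primary outcomes) reports that patient and caregiver engagement "indicated the need for two co-primary outcomes for the clinical trial": the 30-day changes in PROMIS anxiety and in PROMIS informational support.

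Section 2.4 (Power and sample size) computes the size with "a Bonferroni correction for two co-primary outcomes (2-sided alpha 0.025"). Its conclusion reads "1,130 participants (565 participants in each treatment group) are needed for 95% or greater power". The effect that the trial is sized for is given as a "2.5 unit difference (25% of a standard deviation, or T-score of 2.5) for each of the co-primary outcomes". Power is therefore set for each outcome separately.

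Section 2.11 (Analytical and statistical approaches) carries the same level into the analysis: a "2-sided Bonferroni-corrected alpha of 0.025 (and 97.5% confidence intervals, CIs) for the two co-primary outcomes". All other tests use 0.05.

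The two sections agree on the level and on its being two-sided. Neither mentions a step-down or any passing on of alpha once one outcome has been shown.

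**The concern.** Under a flat split, each outcome faces the 0.025 threshold whatever happens to the other. If anxiety is significant at 0.025 and informational support has p = 0.03, the second is declared not significant, although a procedure with the same 5% family-wise error would allow the claim.

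Holm's step-down is that procedure. It needs no assumption about the correlation between the outcomes and no extra participants. Because section 2.4 sets its power goal per outcome, power per outcome is a fair yardstick, and this is where the flat split gives something away.

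**Working it through.** **Inputs.** Two-sided alpha 0.025 per outcome, so 0.05 for the family (sections 2.4 and 2.11). Difference 2.5, equal to 25% of an SD, so SD 10 (section 2.4; section 2.10.1 describes a "standardized T-score with a mean of 50 and standard deviation of 10 for the US general population"). 565 randomised per arm with 20% attrition, so 565 × 0.8 = 452 analysed per arm, which fits the complete-case analysis in section 2.11. The correlation between the two test statistics is not given; it is assumed and varied from 0 to 0.7.

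**The plan's own figure.** SE = 10 × √(2/452) = 0.6652. Power at 0.025 = Φ(2.5/0.6652 − 2.2414) = Φ(1.517) = 93.5%, close to the stated 95%. Power at 0.05 = Φ(2.5/0.6652 − 1.9600) = Φ(1.798) = 96.4%.

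**Holm controls the same error.** If both nulls are true, a false rejection requires the smaller p-value to be at most 0.025, which has probability at most 2 × 0.025 = 5%. If one null is true, it is rejected only when its own p-value is at most 0.05. Neither step uses the correlation.

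**Holm rejects everything Bonferroni rejects.** An outcome with p ≤ 0.025 is either the smaller p-value and rejected at step one, or the larger, in which case step one has already succeeded and it is tested at 0.05.

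**Power per outcome under Holm.** Outcome 1 is rejected if |Z₁| > 2.2414, or if |Z₁| > 1.9600 and |Z₂| > 2.2414. At correlation 0 this can be done by hand:

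- Both differences 2.5: 0.9354 + (0.9639 − 0.9354) × 0.9354 = 0.9621. Both outcomes: 0.9354² + 2 × 0.0267 = 0.928, against 0.875 under Bonferroni.
- Both differences 2.0: power is 0.7779 at 0.025 and Φ(3.0067 − 1.9600) = 0.8524 at 0.05. Holm: 0.7779 + 0.0745 × 0.7779 = 0.836. Both outcomes: 0.7779² + 2 × 0.0580 = 0.721, against 0.605.

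**Correlation 0 to 0.7**, from the bivariate normal distribution:

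| True difference, both outcomes | Quantity | Bonferroni | Holm |
|---|---|---|---|
| 2.5 | power per outcome | 93.5% | 95.5-96.2% |
| 2.5 | power for both | 87.5-89.8% | 92.8-93.7% |
| 2.5 | power for at least one | 97.3-99.6% | identical |
| 2.0 | power per outcome | 77.8% | 82.1-83.6% |
| 2.0 | power for both | 60.5-68.5% | 72.1-77.1% |
| 0 | family-wise error | 4.3-4.9% | identical |

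Power for at least one outcome is identical because Holm's first step is the Bonferroni test.

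**The case against.** The strongest defence is that nothing here is wrong. Bonferroni is valid, applied consistently in sections 2.4 and 2.11, and already paid for in the sample size. If one significant outcome is enough for success, Holm adds nothing to the chance of success. The flat rule also keeps test and interval in step: an outcome is significant exactly when its 97.5% interval excludes zero. All of this stands. It makes the point an improvement and not a correction, and it identifies the price of Holm.

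Three stronger readings are tempting, and the document does not support them.

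- A reader might infer that the Bonferroni split is why power falls short of 95%. It is not: section 2.4 sizes the trial at 0.025. The gap between 93.5% and 95% comes from how attrition enters. At 0.025 and 95% power, 484 per arm are needed; 484/0.8 = 605 and 484 × 1.2 = 581, against the stated 565. Power is 94.5% with 565/1.2 = 471 per arm and 97.5% with all 565. The residual SD of the adjusted model is also not given.
- A reader might treat the lack of an explicit success rule as a defect, since co-primary can also mean that both are required. But alpha, intervals and power are all set per outcome, which largely implies separate claims, and an article may leave the explicit wording to the full protocol or analysis plan.
- A reader might quote the larger gain when the differences are 2.5 and 1.5: the weaker outcome goes from 50.5% to about 61%. A difference of 1.5 lies below the 2 to 5 range that sections 2.4 and 2.10.1 give for the minimal important difference, so it should not carry the argument.

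**Conclusion.** The point holds as a cheap improvement. The planned tests are valid, but for testing they are dominated by Holm at the same 5% family-wise error.

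At the design difference the gain is 2.0 to 2.7 percentage points per outcome and about 4 to 5 points for winning on both. At 2.0, the lower end of the stated important range, it is about 4 to 6 points per outcome and about 9 to 12 points for both. It is zero for winning on at least one.

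These sizes rest on 452 analysed per arm, SD 10, equal true differences on the two outcomes, and a correlation that the document does not state. The dominance itself rests on none of these.

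**What to change.** In section 2.11, before unblinding, replace the flat rule with Holm: compare the smaller of the two co-primary p-values with 0.025 and, if it is significant, compare the other with 0.05, for a family-wise two-sided alpha of 0.05. Keep the 97.5% intervals for estimation. Section 2.4 can stay as it is; its calculation at 0.025 is then slightly conservative, and the sample size does not change.

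Add one sentence saying that significance is read from the Holm p-values. When the second p-value lies between 0.025 and 0.05, the 97.5% interval for that outcome includes zero although Holm rejects, and readers should be told this in advance.

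The cost is a few sentences, with no extra participants or data, and the loss of exact agreement between test and interval in that one case. Timing matters: the same change made after unblinding would look driven by the results.

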## Discussion

3

Although early hospital readmission has recently gained prominence with reimbursement models that include financial penalties to health systems with excess 30-day readmissions by CMS and other payers, the patient and caregiver experience during hospital-to-home transitions had not been extensively studied. MSIs provide a disproportionate share of care to patients who have especially high risk of early hospital readmission, which also tend to be patients with lower socioeconomic resources. Among Medicare beneficiaries, readmission rates are significantly higher for African Americans at MSIs (26%) than whites at non–MSIs (21%) (2,37) These findings suggest that financial penalties for excess hospital readmissions are likely to disproportionately affect MSIs, further limiting their available resources to care for this population. This highlights the need to develop and evaluate low-burden interventions that, if shown to be effective, have the potential for widespread implementation.

Innovative aspects of the PArTNER study include its focus on the patient experience during the hospital-to-home transition, early and continuous stakeholder engagement to inform the design and implementation of the study, and integrating patient advocacy organizations in the delivery of the Navigator intervention (peer coaching).

Results of the stakeholder engagement phase were used to ensure that the Navigator intervention was tailored to the local needs of end-users, including patients, caregivers, front-line clinicians, and health system administrators, and feasible to implement during routine healthcare operations after the completion of the study period.

The study outcomes were selected to address the needs of the multiple stakeholders involved in the design and implementation of the PArTNER study. The primary outcomes were selected to address patient preferences to focus on two measures of patient experience (patient-reported anxiety and informational support). These co-primary outcomes were selected as they are mechanistically directly linked to the intervention procedures, that is, to provide social and informational support. Some of the secondary outcomes, such as the different measures of healthcare utilization, were selected to address the needs by health system administrators regarding unplanned early readmissions. The method of outcome collection, including collection of baseline measures while participants are hospitalized and telephone-based collection of follow-up outcomes, and limiting the number of outcomes that were collected, were designed to minimize participant burden.

The focus on several CMS penalty-sensitive conditions for hospital readmissions (heart failure, pneumonia, COPD, myocardial infarction, and sickle cell disease, a condition with among the highest readmission rates among Medicaid beneficiaries) is potentially relevant to many health systems in the U.S. However, our study was conducted in a single, state-supported MSI with relatively good transitional care services; these factors may limit the external validity of the study findings.

Given the complexity of the Navigator intervention, it is possible that some aspects of the intervention (especially peer coaching) will not be completely implemented in all participants. Although process measures, such as fidelity of implementation of the intervention, will be collected by the study staff, it may not be possible to establish a clear relationship between participant outcomes and the “dose” of the intervention they received. As the intervention is specifically designed to target participants with low socioeconomic resources, another potential limitation is missing outcome data due to inability to reach participants due to unstable housing or telephone contact information.

In summary, the PArTNER study will evaluate the effectiveness of a Navigator intervention led by CHWs and peer coaches that target social determinants of health on stakeholder-supported measures of patient experience and clinical outcomes in patients hospitalized at an MSI. We hope the lessons from the PArTNER study will be of interest to patients and their caregivers, hospital leaders and staff who plan and implement hospital-to-home transitional care services at MSIs, as well as payers and policymakers interested in promoting more effective care transitions in high-risk populations.

